## Methods: participants, interventions, and outcomes

### Study setting {9}

This trial is conducted at a single center, specifically at the Department of Cardiac Surgery, Nanjing Drum Tower Hospital. Nanjing Drum Tower Hospital serves as a prominent heart center in Nanjing city, located in Jiangsu province, China. Inclusion criteria, as delineated below, are applied to assess the eligibility of patients for recruitment into the study.

### Eligibility criteria {10}

The inclusion criteria are as follows:Patients diagnosed with aTAAD require emergency operation;Patients aged between 18 and 65; andSigning an informed consent.

The exclusion criteria are as follows:Long-term fasting or inability to self eat;History of malignant tumors;Weight < 50 kg;Traumatic aortic dissection;Patients with Marfan syndrome;Unstable vital signs require mechanical assistance or rescue before surgery (IABP, ECMO, LVAD, etc.);Patients required endotracheal intubation before surgery;After admission, patients with consciousness disorder, central nervous system dysfunction, or evidence of cerebral hypoperfusion;Preoperative hematemesis, black or bloody stools, or bowel dilation;Limb ischemia before surgery;Malperfusion syndrome before surgery;Patients who need percutaneous interventions to relieve malperfusion;History of digestive ulcer or chronic gastroenteritis;Dialysis before admission or a history of renal insufficiency;History of liver disease;Allergies to aspirin and non-steroidal anti-inflammatory drugs like ketorolac tromethamine;Chronic inflammatory diseases, autoimmune diseases, or other situations require long-term use of hormones or non-steroidal drugs;No cerebral perfusion during deep hypothermic circulatory arrest;History of Grade 4 surgery or acute myocardial infarction within 90 days;History of cardiac surgery or operations on great vessels;Pregnant and lactating women;Refusing to participate in this clinical trial or sign an informed consent form;Other situations where the subject deems it unsuitable to participate in this project.

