**Methods/design:**

This study is a single-center, randomized, double-blinded, and placebo-controlled study. A total of 120 patients with aTAAD will be recruited and will be randomized into the ketorolac group and placebo group with a ratio of 1:1. Ketorolac tromethamine 60 mg per 2 ml will be intramuscularly injected within 2 h before surgery, followed by intramuscular injections of 30 mg per 1 ml BID. on the first and second postoperative days in the Ketorolac group, while 0.9% saline will be administered at the same dose, dosage form, and time in the placebo group. This study aims to evaluate the safety and efficacy of ketorolac in improving the prognosis of aTAAD. The primary endpoint is the composite endpoint event concerning drug-related adverse events. Secondary endpoints include drug-related adverse events, laboratory examination of blood, diagnostic imaging tests, clinical biomarkers, etc.

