### Who will take informed consent? {26a}

Patients diagnosed with aTAAD and planning to undergo surgical treatment will undergo eligibility screening to determine their suitability for participation in this trial. Once the surgeon has assessed the patient as eligible, their family will be invited to meet with the research physician. During this meeting, their family will have the opportunity to ask any questions they may have and sign the informed consent form.

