### Intervention description {11a}

The surgeries will be performed by [name]. The study will commence on the day the patients sign an informed consent form and receive their randomized numbers. The ketorolac group, consisting of patients with aTAAD, will be treated with ketorolac. They will receive a preoperative intramuscular injection of 60 mg per 2 ml ketorolac and a postoperative injection of 30 mg per 1 ml ketorolac BID for two consecutive days. The placebo group, also consisting of patients with aTAAD, will receive placebo treatment. They will receive a preoperative intramuscular injection of 2 ml 0.9% saline placebo and a postoperative injection of 1 ml 0.9% saline placebo BID for two consecutive days. During the administration of ketorolac, patients’ blood pressure and renal function will be routinely monitored, and targeted treatment methods such as sedation, hypotension, diuresis, and dialysis will be applied as necessary. Additionally, all included patients will receive the same medical and surgical treatments in accordance with the diagnosis and treatment guidelines for aTAAD. Aortic dissection tissue samples will be collected for laboratory study during the surgery. Both the ketorolac group and the placebo group patients will undergo follow-up examinations before surgery and on the 1st, 3rd, 5th, 7th, 30th, and 90th day after surgery. These examinations will include assessments of adverse drug events, cardiac ultrasound, chest X-ray, laboratory tests (blood routine examination, blood biochemistry, erythrocyte sedimentation rate, coagulation function, CK-MB, cardiac troponin I (cTnI), PCT, IL-6, CRP, myohemoglobin (MYO), type B natriuretic peptide (BNP), D-dimer, etc.) and clinical biomarkers (matrix metalloproteinase-9 (MMP-9), MMP-2, MMP-3, MMP-13, type III procollagen, etc.). CTA examination of the cervical, thoracic, and abdominal aorta artery will be performed before surgery and on the 30th and 90th days after surgery.

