### Sample size {14}

The required sample size was calculated using the PASS (15.0.5) software. The primary endpoint of efficacy was used to calculate the sample size. In the literature, the total death rate of hospitalization after surgery was 25% [7], the incidence of organ malperfusion syndrome was 15–33% [19, 20], permanent dialysis was 2.6% [21], tracheotomy was 8% [22], neurological impairment was 6.9% [22], postoperative mechanical circulatory support was 20% [23], unplanned cardiac reoperation was 4.2% [24], and postoperative cardiac arrest was 0.7–5.2% [25]. Therefore, we assumed that the incidence of composite endpoint events in the control group is 70%, and the incidence of composite endpoint events in the ketorolac group is reduced to 40%. Using PASS (15.0.5) software, when the sample size of the ketorolac group and the control group is 53 cases, this difference can be detected with over 90% confidence. Considering that the loss of follow-up rate is higher than 10%, the final total sample size of this experiment is 120 cases, with 60 cases in the experimental group and 60 cases in the control group.

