## Statistical methods

### Statistical methods for primary and secondary outcomes {20a}

Statistical analysis will be performed using SPSS software (version 26.0) and R (× 64 3.5.0). Continuous variables will be presented as mean ± standard deviation. The Kolmogorov–Smirnov test will assess normal distribution. If variables exhibit normal distribution, an independent sample *t*-test will be employed; otherwise, the Mann–Whitney *U* test will be utilized. Categorical variables’ frequency will be expressed as percentages and analyzed using the chi-square test or Fisher’s exact test. It should be noted that we are not conducting an Intention to Treat analysis due to the exclusion of patients with more than 10% missing data. Double-tailed *p*-values and 95% confidence intervals will be reported, with statistical significance defined as *p* < 0.05.

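### An exclusion criterion worded as an event during circulatory arrest can, read literally, be confirmed only after randomisation and the first injection, and nothing stated keeps such patients in the analysis

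*Protocol article*

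**What the plan says.** The exclusion list in Eligibility criteria {10} includes "No cerebral perfusion during deep hypothermic circulatory arrest". It has no qualifier such as planned, intended or expected.

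The rest of the article places recruitment before the operation:

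- Who will take informed consent? {26a}: "Once the surgeon has assessed the patient as eligible, their family will be invited to meet with the research physician". Eligibility is settled before consent.
- Intervention description {11a}: "The study will commence on the day the patients sign an informed consent form and receive their randomized numbers".
- Abstract, Methods/design: the first dose "will be intramuscularly injected within 2 h before surgery".
- Table 1 (Participant timeline {13}) marks the eligibility screen, randomisation and first study drug before surgery, and puts surgery in the post-allocation period. The eligibility screen is marked once.

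On the analysis population, Statistical methods {20a} states that "we are not conducting an Intention to Treat analysis due to the exclusion of patients with more than 10% missing data".

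**The concern.** An exclusion criterion should be decidable before a patient is randomised. This one, as worded, describes something that happens on the operating table. A patient who meets it has by then been allocated and injected. To follow the criterion is to take that patient out after randomisation, on the basis of how the operation went.

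Randomisation makes the two arms comparable as randomised. Removing patients on an event after allocation leaves a comparison that randomisation no longer protects. If the event is related to outcome, primary endpoint events are removed along with the patients. The primary efficacy composite (Outcomes {12}) includes death and neurological impairment, so a criterion about perfusion of the brain is not obviously unrelated to it. The documents do not quantify any such relation, and the point does not depend on one.

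An all-randomised analysis would contain the problem, because an ineligible patient would still be counted. This plan declines that analysis, so the ambiguity is left without a safeguard.

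**Working it through.** **1. Order of events.** From {26a}, {11a}, the Abstract and Table 1, the sequence is:

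1. eligibility screen by the surgeon
2. consent
3. randomisation
4. first injection, at most 2 h before surgery
5. operation, including circulatory arrest
6. only then is it known whether cerebral perfusion was given during the arrest

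The criterion belongs to step 1 but, taken literally, is observed at step 6.

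**2. Comparison with neighbouring criteria.** Several other exclusions in the same list are tied explicitly to the preoperative period: mechanical assistance or rescue, intubation, gastrointestinal signs, limb ischaemia and malperfusion syndrome. This one is tied to the arrest itself.

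**3. What happens to such a patient.** The discontinuation reasons in {11b} do not name this situation. {20a} and {20c} delete patients with more than 10% missing data, and {17b} treats emergency-unblinded subjects as withdrawals. None of these sections says whether a randomised patient who meets the criterion in theatre stays in or comes out. The auditing section {23} has a monitor check inclusion and exclusion criteria in 25% of patients, so such a case could surface as an eligibility violation with no stated handling.

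**4. The plan's own sample size.** Inputs from Sample size {14}: 70% with an event in the control group and 40% in the ketorolac group. The article says that "this difference can be detected with over 90% confidence", which I take to mean power. From {20a}: two-sided 5% significance. Allocation is 1:1.

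Two-proportion Z test, unpooled variance:

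n = (1.960 + 1.282)² × (0.7 × 0.3 + 0.4 × 0.6) / 0.3² = 52.5, so 53 per arm (power 90.2% at 53).

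This reproduces the stated 53. The pooled version of the test needs 56 per arm and has 88.5% power at 53.

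**5. The margin for losses.** 120 − 2 × 53 = 14 patients, which is 14/120 = 11.7%. Section {14} assigns it to loss to follow-up only.

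**6. Size of the added loss.** The documents give no frequency, so 5% to 10% is an assumption.

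- 5% of 120 = 6 patients; 6/14 = 43% of the margin.
- 10% of 120 = 12 patients; 12/14 = 86% of the margin.

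**7. Effect on power.** Pooled two-sided test, 60 randomised per arm, 10% loss to follow-up, with this exclusion on top:

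Power = Φ{ [0.3√n − 1.960 √(2 × 0.55 × 0.45)] / √(0.21 + 0.24) }

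| Assumed share excluded | Evaluable per arm | Power | Per arm needed to keep 53 |
|---|---|---|---|
| 0% | 60 × 0.90 = 54.0 | 89.1% | 59 |
| 2% | 54.0 × 0.98 = 52.9 | 88.5% | 61 |
| 5% | 54.0 × 0.95 = 51.3 | 87.4% | 62 |
| 10% | 54.0 × 0.90 = 48.6 | 85.6% | 66 |
| 20% | 54.0 × 0.80 = 43.2 | 81.2% | 74 |

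The last column is 53 / (0.90 × (1 − share)), rounded up. In the 5% to 10% range, the power loss is about 2 to 4 percentage points.

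**The case against.** The strongest reply is that the criterion was meant as the perfusion strategy the surgeon intends. The surgeon assesses eligibility before consent, and Table 1 shows a single preoperative screen with no later re-screen. On that reading the criterion can be screened in advance, and nobody need be removed after randomisation. This is a reasonable reading and it stands as a possibility. The wording does not say it, however, and a plan can change in theatre, a case on which the article is silent.

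A second reply is that a condensed article may leave the handling of patients found ineligible to the full protocol or analysis plan. That is fair as far as the missing rule goes. The point here is about what the article does state: a criterion anchored to the operation, and an analysis declared not to be intention to treat.

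A third reply is blinding. Patients and study staff do not know the allocation ({16b}, {17a}), so exclusion that differs by arm is less likely. This is correct and lowers the concern. It does not rule out a difference, because the first dose precedes the event.

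Three stronger conclusions might be inferred, and the documents support none of them:

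- **That treated patients have been, or certainly will be, removed.** No section says so. Trial status reports only that fifty-five patients had been included by 20 March 2024.
- **That the injection alters the perfusion decision, or that patients without cerebral perfusion carry a known excess risk.** Neither is stated in the article.
- **That these exclusions would use up the whole loss margin.** At the assumed 5% to 10% they take 43% to 86% of it.

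**Conclusion.** The point holds in a limited form. The criterion is worded so that, read literally, it can be confirmed only after randomisation and the first injection. Applying it that way would exclude randomised patients on operative course, and nothing stated in the analysis keeps them in. Whether this happens depends on which reading the investigators follow.

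The size is uncertain. At an assumed 5% to 10%, 6 to 12 of 120 patients would go, and power on the pooled test would fall from 89.1% to between 87.4% and 85.6%, given 10% loss to follow-up and the plan's own event rates. Departure from the randomised comparison matters more than this loss of power. The rejection of intention to treat in {20a} is a broader issue in its own right; it matters here because it removes the usual safeguard.

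The wording should be corrected, and early: fifty-five patients were already in by 20 March 2024, and the interim analysis ({21b}) is set at 60.

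**What to change.** 1. Restate the criterion as the planned perfusion strategy, recorded before randomisation, or remove it from the exclusion list.
2. State that a randomised patient whose perfusion in theatre differs from the plan stays in the primary analysis, in the arm to which the patient was allocated.
3. Report intraoperative cerebral perfusion descriptively by arm.
4. Check whether any enrolled patient has been excluded on this ground. If so, recover the data and restore that patient to the analysis.

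The cost is an amendment to the eligibility wording, one sentence on the analysis population, and data recovery only if a case is found. The downside is a slightly more heterogeneous population. No treatment or surgical technique changes, and this criterion then adds nothing to the losses, so it calls for no increase over the planned 60 per arm.

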#### Secondary endpoints

Erythrocyte sedimentation rate (ESR), C-reactive protein, procalcitonin, SII [17], coagulation function (prothrombin time, activated partial prothrombin time, bleeding time), liver function (alanine transaminase, glutamic transaminase, lactate dehydrogenase, total bilirubin, direct bilirubin), renal function (creatinine, uric acid, eGFR), high-sensitivity troponin T, serum B-type natriuretic peptide, myocardial enzyme (creatine kinase, creatine kinase MB isoenzyme), and other laboratory examination of blood;Chest X-ray (for pulmonary inflammation and effusion, etc.), CTA scan of the cervical, thoracic, and abdominal aorta artery (for aortic diameter and extent of dissection, etc.), cardiac ultrasound (for cardiac ejection fraction and left ventricular diastolic dysfunction, etc.), and other imaging examinations.The patient’s cardiopulmonary bypass time during surgery, total surgical time, aortic cross-clamping time, and postoperative hospital stay;Postoperative drainage color, drainage volume, postoperative patient blood transfusion, and transfusion volume;The incidence of postoperative sternal infection, secondary debridement, secondary tracheal intubation, pneumonia, and delirium; andEnzyme-linked immunosorbent assay (ELISA) will be performed to detect and measure IL-1β IL-2, IL-4, IL-6, IL-8, IL-10, IL-12, IL-13, TNF-α, INF-γ, granulocyte–macrophage colony-stimulating factor (GM-CSF) and calcitonin;

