### Participant timeline {13}

Table 1 shows the participant timeline.

**Table 1 Tab1:** Participant timeline

	Study period								
	Enrolment	Allocation	Post-allocation						Close-out
Timepoint	Before surgery	Before surgery	During surgery	Postoperative day 1	Postoperative day 3	Postoperative day 5	Postoperative day 7	Postoperative day 30	Postoperative day 90
Enrolment									
Informed consent	** × **								
Eligibility screen	** × **								
Allocation		** × **							
Randomization		** × **							
Interventions									
Tissue samples collection			** × **						
Ketorolac tromethamine		** × **		** × **	** × **				
0.9% saline		** × **		** × **	** × **				
Assessments:									
Vital signs	** × **		** × **	** × **	** × **	** × **	** × **	** × **	** × **
Hematology examination	** × **		** × **	** × **	** × **	** × **	** × **	** × **	** × **
CTA scan of cervical thoracic and abdominal aorta artery	** × **							** × **	** × **
Chest X-ray				** × **	** × **	** × **	** × **	** × **	** × **
Echocardiography	** × **				** × **			** × **	** × **
Adverse events	** × **		** × **	** × **	** × **	** × **	** × **	** × **	** × **
Complications	** × **		** × **	** × **	** × **	** × **	** × **	** × **	** × **

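### The exclusion list names no known bleeding disorder and no current anticoagulant or P2Y12-inhibitor treatment, and its only catch-all is worded for the subject, so some patients with impaired hemostasis could meet every printed criterion

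*Protocol article*

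**What the plan says.** Protocol article, Eligibility criteria {10}, prints 23 exclusions. Several limit bleeding risk, most directly "Preoperative hematemesis, black or bloody stools, or bowel dilation". Others remove patients with a past ulcer or chronic gastroenteritis, liver disease, renal insufficiency or dialysis, or a condition needing long-term hormones or non-steroidal drugs. None names a bleeding disorder, a low platelet count, or treatment with an anticoagulant or P2Y12 inhibitor.

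The last two items bear on who decides. One excludes patients for "Refusing to participate in this clinical trial or sign an informed consent form". The other, the only catch-all, reads "Other situations where the subject deems it unsuitable to participate in this project".

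On process, section {26a} says that patients "will undergo eligibility screening to determine their suitability for participation in this trial", and that the surgeon assesses eligibility before the family is approached. Section {11a} plans "laboratory tests (blood routine examination, blood biochemistry, erythrocyte sedimentation rate, coagulation function" and further tests before surgery and at follow-up. The participant timeline marks "Hematology examination" in the enrolment column. Under Secondary endpoints, the article lists "coagulation function (prothrombin time, activated partial prothrombin time, bleeding time" and other laboratory measures as outcomes.

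On exposure, the Methods/design part of the abstract says that the first dose, 60 mg, "will be intramuscularly injected within 2 h before surgery".

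**The concern.** The protocol itself treats bleeding as a main hazard. The Safety assessment section lists gastric bleeding among ketorolac's main adverse reactions. The safety part of the primary endpoint counts gastrointestinal bleeding, and bleeding above 1000 ml in the first 24 hours after the operation. The monitoring committee section calls the study high-risk.

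The largest single dose comes just before emergency aortic surgery, so the entry criteria are the main safeguard against giving it to someone who already bleeds easily. The discontinuation rules {11b} and emergency unblinding {17b} act on patients already in the study, and the monitoring board {21a} reviews accumulated data. By then the preoperative dose may already have been given.

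An investigator-judged catch-all would normally cover what a list leaves out. As printed, this one does not, because it hands the judgement to the subject. What is at stake is patient safety at entry, not the validity of the randomized comparison.

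**Working it through.** The plan gives no figure on this point, so there is none to reproduce. The check is a reading of the text, followed by arithmetic on exposure and on the reach of an amendment.

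**1. Who passes the printed list.**
- Liver disease, renal insufficiency or dialysis, and long-term non-steroidal use are excluded. These remove some patients with impaired hemostasis.
- Recent myocardial infarction or Grade 4 surgery (within 90 days) and any earlier cardiac or great-vessel surgery are excluded. By clinical inference, these remove some users of antiplatelet or anticoagulant drugs.
- Still passing: a patient with a known bleeding disorder and no overt gastrointestinal bleeding, or one taking an anticoagulant or P2Y12 inhibitor for a reason outside those exclusions.

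**2. Whether another section closes the gap.**
- {26a}: the surgeon screens for suitability, but no bleeding ground is stated.
- {11a} and the timeline: the tests are planned before surgery, but no result is tied to entry.
- Secondary endpoints: coagulation is an outcome there, not a criterion.
- {11d}: all patients receive the same guideline care; antithrombotic drugs are not mentioned.
- {11b}: covers stopping after entry.

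None of these ties a bleeding ground to entry.

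**3. The catch-all.** Refusal already has its own item immediately before it. A subject-judged catch-all would add almost nothing, which supports reading it as a slip for the investigator.

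**4. Exposure in the ketorolac group.** 60 mg + 2 days × 2 doses × 30 mg = 180 mg in total. The preoperative share is 60/180 = 33%.

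**5. Reach and cost of an amendment.** Inputs from Trial status and Recruitment {15}: start in August 2023 (taken as the 1st), 55 enrolled by 20 March 2024, target 120, end in December 2026.
- Accrual: 232 days = 7.62 months; 55/7.62 = 7.22 per month.
- Not yet enrolled on that date: 120 − 55 = 65. At 7.22 per month these take 65/7.22 = 9.0 months.
- If the amendment takes m months (an assumption), those left are 65 − 7.22m:

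| m | Left to enrol | On ketorolac (half) | Enrolled under old list | Share of 120 |
|---|---|---|---|---|
| 1 | about 58 | about 29 | about 62 | 52% |
| 2 | about 51 | about 25 | about 69 | 58% |
| 3 | about 43 | about 22 | about 77 | 64% |

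- The interim at 60 patients: 5/7.22 months = about 21 days after 20 March 2024, so all interim patients would probably fall under the old list.
- Accrual slack to 31 December 2026: 33.4 months remain; 65/33.4 = 1.95 per month needed; 1 − 1.95/7.22 = 73% of eligible patients could be lost before the date slips.
- Trial status also gives a two-year duration. Counted from August 2023 (end of July 2025), 16.4 months remain; 65/16.4 = 3.97 per month; tolerated loss 1 − 3.97/7.22 = 45%.
- If recruitment began on 31 August 2023 instead, accrual is 8.29 per month, about 57, 48 or 40 are left after one, two or three months, and the tolerated losses are 77% and 52%.

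**The case against.** The strongest reply is that the gap depends on reading a slip literally. With the investigator in place of the subject, the last item would allow exclusion for any unlisted bleeding risk, and {26a} already writes in a clinician's assessment of suitability. This largely stands. A reader might infer that nobody can keep such a patient out, or that entry rests on a wholly unwritten judgement; the documents do not support that. What remains is that the operative text is wrong as printed, and that even the corrected catch-all would name no bleeding ground.

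A reader might also infer that any patient with impaired hemostasis meets every criterion. That is too strong, since several printed exclusions remove some of these patients. Only *some* could pass.

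It can further be said that the proposed exclusions rest on clinical judgement. The document nowhere says that ketorolac interacts with anticoagulants or P2Y12 inhibitors, or sets a platelet limit for its use. That is fair: the bleeding endpoints show that the risk matters, not which groups must be excluded. It is a reason to have the sponsor and the monitoring board confirm the drug list.

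Finally, an article condenses a protocol, and the full version may contain more. The list is long and specific, so it does not look abridged, but this cannot be ruled out. It would not excuse the wrong word in an item that is printed.

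**Conclusion.** The point holds in a limited form. The printed list names no known bleeding disorder and no current anticoagulant or P2Y12-inhibitor treatment, and its only catch-all is worded for the wrong party. Some patients with impaired hemostasis could meet every printed criterion and receive 60 mg of ketorolac before emergency surgery.

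The number of such patients is unknown. The 65 not yet enrolled on 20 March 2024 are a ceiling on how many could be screened under a new list. A reader might take 65 as the number who would benefit, but only those with impaired hemostasis could, and the documents do not allow a count.

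No bias is claimed, and nothing here affects the randomized comparison. The conclusion assumes that the article prints the full list and that the named conditions and drugs raise bleeding risk around surgery, which is a clinical judgement. The weight is modest: a cheap safety improvement worth making.

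**What to change.** Two changes to Eligibility criteria {10}:

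- Reword the last exclusion so that the investigator, not the subject, judges whether a subject is unsuitable.
- Add one exclusion: known bleeding disorder, or current treatment with an anticoagulant or P2Y12 inhibitor. Screen for it from the drug history and from the blood routine and coagulation tests already planned before surgery. The sponsor and the monitoring board should confirm the drug list.

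Add a platelet or coagulation limit only with a numeric threshold agreed by the sponsor and the monitoring board. Naming thrombocytopenia without a number would leave the same room for interpretation.

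Apply the changes only to patients not yet enrolled, and report how many entered under each version.

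The cost is one amendment and no new tests. Accrual would be slightly slower, with ample slack at the observed rate. Applicability would be somewhat narrower, and the criteria would change partway through enrolment. At the observed rate the remaining enrolment takes about nine months, so the change is useful only if made promptly.
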